#### **9.8. Trial design diagram:**

[figure not shown]

## 10. SELECTION AND WITHDRAWAL OF SUBJECTS

### 10.1. Inclusion criteria:

Subjects eligible to be enrolled in this trial must be adults older than 18 years and younger than 50 years, weighing more than 40 kg, with a conventional confirmatory serology for *T. cruzi* infection from the Instituto de Salud Pública de Chile (ISPCH). A positive qPCR will be selected to participate in this trial. Only patients with a new diagnosis of Chagas disease in the chronic indeterminate phase will be included. In addition, they must have normal values in laboratory tests for the following parameters: total white blood cell count, platelet count, creatine kinase (CK), alanine aminotransferase (ALT), aspartate aminotransferase (AST), total bilirubin or creatinine, or a gamma-glutamyl transferase (GGT)  $\leq 2$  times the upper limit of normal (X ULN); Women of reproductive age must have a negative serum pregnancy test, must not be breastfeeding, and must consistently use a highly effective method of contraception throughout the treatment phase.

Subjects must also meet all the following criteria: the ability to comply with all tests and follow-up visits specified in the protocol and have a permanent address; sign the written informed consent form.

### 10.2. Exclusion criteria:

Signs and symptoms of the digestive form of CD; stage II or higher chronic cardiac CD; acute or chronic health conditions such as acute infections, history of HIV infection, diabetes, liver and kidney disease; pre-existing heart disease unrelated to Chagas disease; hypothyroidism, and family history of muscle disorders; formal contraindication to receiving NFX or BZD, known history of hypersensitivity, allergy or severe adverse reactions to ATO, BZD or NFX; history of prior treatment

for CD; history of previous treatment with atorvastatin, lovastatin, rosuvastatin, simvastatin or any other statin; any concomitant use of antimicrobial agents; history of alcohol or drug abuse; any condition that precludes oral medication; concomitant or intended use of CYP3A4 modifiers; a medical history of familial short QT syndrome or concomitant therapy with drugs that may shorten the QT interval. Abnormal laboratory test values for the following parameters: total white blood cell count, platelet count, creatine kinase (CK), alanine aminotransferase (ALT), aspartate aminotransferase (AST), total bilirubin or creatinine, or a gamma-glutamyl transferase (GGT) > 2 times the upper limit of normal (X ULN); Pregnant or lactating women; refusal to use a highly effective method of contraception during the treatment phase.

Patients meeting the selection criteria will undergo the randomization procedure. Only subjects enrolled in this trial will receive the study drugs. Patients will be assigned, in ascending order, a trial identification number (TIN) according to the enrollment order. A patient is considered randomized when s/he receives a TIN.

## **11. Subject treatments**

### **11.1.1. Doses and treatments regimens**

Tablets of 40 and 80 mg of ATO will be purchased from a pharmaceutical laboratory with current sanitary registration recognized by the ISPCH, offering the active ingredient in a bioequivalent formulation. The placebo tablets will correspond to a nutritional supplement tablet supplied by a registered provider.

The purchase will be made through the Pharmacy of the Clinical Hospital of the University of Chile.

The ATO and placebo tablets will be repackaged in black plastic bottles of 200 ml capacity, previously sterilized with UV light, under aseptic conditions using a type II biosafety hood. The bottles will contain 120 tablets each and all from the same lot to allow the traceability of the drug.

The labeling of each bottle will be done as required by good manufacturing practices, including a) name and contact information (telephone and e-mail) of the principal investigator; b) dosage form, route of administration, number of units; c) lot number and code (assigned by the principal investigator) of the supplier laboratory; d) project code; e) instructions for use; g) randomization code; f) warning: "for clinical trial use only"; h) expiration date; i) the phrase: "Keep out of the reach of children."

The antichagasic drugs NFX or BZD will be supplied by the Chilean Ministry of Health as part of the PCC. The antichagasic treatment will be administered according to the indications of the "Manual de Procedimientos para la Atención de Pacientes con Chagas" (MINSAL, 2017), and the administration of ATO, antichagasic drugs, and placebo treatment will be monitored at each of the patients' visits to determine tablet accounting and compliance with the drugs. BZD dosing will be 5 mg/kg/day every 12 hours (BID), and NFX dosing will be 5-10 mg/kg/day BID. ATO doses will be 40 and 80 mg/day for each group and will be administered in the morning.

At each visit, the patient will be required to bring all remaining study medications at the 30th, 60th, 120th, and 180th-day visits to check compliance with the prescribed antichagasic and experimental treatment and perform medication accounting (Torrico et al., 2018). **If a subject develops**

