## 9.3. Study description:

This is a proof-of-concept Phase II clinical trial with three different groups: Two groups will receive antichagasic therapy plus 40 or 80 mg/day of ATO. The third group will receive a placebo plus antichagasic therapy. The placebo is justified as long as the patient receives the complete conventional antichagasic treatment; therefore, the management of his Chagas disease is assured. In this clinical trial, the placebo will be a nutritional supplement tablet with an appearance similar to that of ATO. This product was chosen given the potential difficulties in manufacturing a small number of pills since the trial does not have a pharmaceutical industry sponsor capable of manufacturing it under Good Manufacturing Practice standards.

Nutritional supplements do not affect vascular or cardiac inflammatory parameters and therefore do not introduce confounding elements in the comparative analysis with atorvastatin.

Patients will first receive conventional antichagasic therapy for two months. After two weeks (or until normalization of liver enzymes), treatment with atorvastatin or placebo will be initiated for

four months. These doses were chosen to minimize false negative results, thus providing the best hypothesis test and maximizing the pharmacodynamic effect on inflammation and cardiac and endothelial function. In addition, the treatment sequence aims to minimize adverse reactions that could be caused by the eventual combination of antichagasic drugs with atorvastatin. Study subjects will be randomized, and the three groups will be double-blinded (both clinical investigators and subjects will be blinded) to ATO or placebo. However, antichagasic therapy will be open-labeled. In addition, qPCR and the other laboratory evaluations, as well as ECGs and 2D echocardiograms, will be performed with the clinical investigators blinded to ATO or placebo allocation.

This study will be conducted in four centers: 1) Hospital San Juan de Dios and 2) Hospital Felix Bulnes in Santiago, Metropolitan Region, 3) Hospital [name] in Viña del Mar, 4) Hospital San Martin de Quillota, Valparaiso Region. Each center annually admits 60 new patients to its Chagas Control Program (CCP). These four centers are part of the care network of the National Chagas Disease Control Program.

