#### **12.2. Randomization and treatment allocation:**

A computer-generated randomization list will be prepared and stratified by center using a block size of twelve. Each center will receive a list of randomization numbers and corresponding ATO or placebo packages. After patient enrollment, the following randomization number available at the

center will be assigned (in chronological order), and the corresponding treatment package will be delivered.

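### Bottle labels must show a lot number, supplier code and expiry date with no masking step, so blinding and allocation concealment are not secured as written

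*Protocol*

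**What the plan says.** Protocol section 9.3 states that "the three groups will be double-blinded (both clinical investigators and subjects will be blinded) to ATO or placebo"; the summary says the same.

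Section 11.1.1 describes the supply. For the active arms, "Tablets of 40 and 80 mg of ATO will be purchased from a pharmaceutical laboratory with current sanitary registration". For the control arm, "The placebo tablets will correspond to a nutritional supplement tablet supplied by a registered provider". Everything is repackaged into black bottles, and "The bottles will contain 120 tablets each and all from the same lot to allow the traceability of the drug". Among the required label items are "c) lot number and code (assigned by the principal investigator) of the supplier laboratory; d) project code; e) instructions for use; g) randomization code"; item h) is an expiration date. The section presents the list as a good manufacturing practice requirement. Patients bring their remaining medication to the visits on days 30, 60, 120 and 180.

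Section 12.2 specifies blocks of twelve, stratified by centre. "Each center will receive a list of randomization numbers and corresponding ATO or placebo packages", and the next number is assigned in chronological order after enrolment.

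The protocol does not say that the lot number, supplier code or expiry date is masked, made common to the arms or made unique to each bottle.

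**The concern.** A label item that takes one value per product is a marker of treatment group. The label rule in 11.1.1 serves traceability, and a lot number that traces to its maker cannot be common to three different products. Followed literally, the rule lets anyone who handles several bottles at a centre sort them into groups, which conflicts with the double blind in 9.3.

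Two protections are at stake. The first is allocation concealment: if someone involved in enrolment can see the next package, its label may reveal the next group before the patient is enrolled. The second is blinding after randomization. Under 11.2.1 the clinical investigator judges whether a laboratory change is clinically significant. Under 11.2.4 the investigator judges whether an event is drug-related and whether treatment is suspended, resumed or stopped. Knowledge of the arm can influence these judgments.

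**Working it through.** The protocol gives no figure to reproduce. The check sets the label rule beside the supply and the randomization, and then sizes what could be inferred.

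**Step 1: what each label item can separate**

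| Item | If it takes its natural value | If masked or made unique |
|---|---|---|
| Lot number | Differs between ATO 40 mg, ATO 80 mg and the supplement: at least three groups | No information |
| Supplier code | One value per supplier: ATO versus placebo, two groups only | No information, but only if it is not fixed per supplier |
| Expiry date | May differ between products; the text does not say | No information if common to all arms |

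The words in parentheses in item c) can apply to the code alone, or to both lot number and code. On the first reading the maker's lot is printed. On the second, the lot number could be a trial-assigned value that reveals nothing, but the text does not say so. It also describes no linking list, which traceability would then need.

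**Step 2: who handles labels.** Section 12.2 places the numbered packages at the centre. Patients return medication under 11.1.1. ATO or placebo starts after two months of antichagasic treatment and a two-week gap, so at the earliest around day 60 + 14 = 74. The day-120 visit is therefore normally the first at which these bottles come back in use.

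**Step 3: from groups to named arms.** Sorting alone gives unnamed groups. The protocol contains two possible further clues. One is an emergency opening of the blind (11.2.6), which would name the lot of the patient concerned. The other is the lipid profile, part of the laboratory panel scheduled at every visit (9.6); section 7.2 itself notes that ATO is used to lower LDL. One patient's LDL is noisy, but a shared lot number would allow staff to pool patients.

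**Step 4: predictability of the next allocation.** Inputs: block of 12 (12.2) and equal groups of 100 (Summary), so 4:4:4 within a block. The last two rows suppose that the next label is visible and that its meaning has been worked out.

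- No label information: 4/12 = 33.3% correct.
- Supplier code only, with 40 or 80 mg guessed at random: (4 + 8 × 1/2)/12 = 8/12 = 66.7%.
- Lot differs by product and the groups have been identified: 12/12 = 100%, an upper bound.

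A different quantity is the success rate when only past arms are known and the group with most places left is guessed. With n = a + b + c places left, the expected number of correct guesses is f(a,b,c) = max(a,b,c)/n plus the average of f over the possible next draws. Exact enumeration gives f(4,4,4) = 6.14, and 6.14/12 = 51.2%. This reflects the fixed block; labels matter to it only as a route to knowing past arms.

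**Step 5: patients exposed once one group is named.** Inputs: 300 patients, four centres, three arms. Assuming equal recruitment, 300/4/3 = 25 per arm per centre, so 25 − 1 = 24 others if one lot serves the arm there. With two lots of about equal size, 25/2 = 12.5, so 11 or 12 others.

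**The case against.** The strongest reply is that the investigator may assign both the lot number and the code, in which case the printed values could be masked already. The English also reads as a translation, so fine syntax is weak evidence. This stands as a limit: the document does not prove that a maker's lot is printed. It does not remove the point, because a code fixed per supplier would still separate ATO from placebo, and a fully masked scheme is nowhere described.

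Other parts of the reply also stand. Opaque bottles hide the tablets before dispensing. Opening the blind is confined to rare cases and is decided by the treating physician. Much of eligibility rests on laboratory results, which narrows the room for selective enrolment. Section 12.2 delivers the package after enrolment and does not say who stores the stock. The sentence on lots can mean one lot per bottle, and with recruitment planned over 24 months an arm may use several lots.

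A reader might go further, in ways the documents do not support:

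- That the label by itself discloses all three arms. It gives groups, and naming them needs a further clue; a supplier code gives two groups at most.
- That one unblinding exposes the 99 others in an arm of 100. That count is trial-wide and assumes one lot per arm everywhere, whereas staff see their own centre's bottles.
- That patients could sort one another. Nothing suggests that a patient sees more than his or her own bottle.
- That the person reading the label also stages the cardiomyopathy. The protocol does not say who does the staging, and 9.3 has ECG and echocardiography performed with clinical investigators blinded.

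**Conclusion.** The label specification lists identifiers that can be specific to an arm and states no step to mask them. Blinding and allocation concealment are therefore not secured as written; a failure of either is not demonstrated.

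That a maker's lot number would differ between three distinct products is close to certain. That expiry dates differ, that one lot serves a whole arm, and that enrolling staff see the next package are inferences. If the label does separate products and one group becomes named, about 24 further patients at a centre are exposed, assuming equal recruitment and one lot per arm there. Prediction of the next allocation could rise from 33.3% to 66.7% with a supplier code alone, or to at most 100% with lots matched to arms. The matter should be settled before bottles are labelled, because blinding lost through dispensed labels cannot be restored.

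**What to change.** In section 11.1.1, replace items c) and h) on the patient label with:

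- a unique, non-repeating kit number;
- one trial batch code common to all three arms;
- one common expiry date, the earliest of the three products.

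State that the repackaging pharmacy keeps a confidential list linking each kit to its supplier, lot and true expiry, which preserves traceability. State also that codes are assigned by unblinded pharmacy staff and not by the principal investigator, who receives serious adverse event reports and whose own blinding status the protocol does not give.

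In section 12.2, state that centres receive kit numbers only, without the arm.

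The cost is a revised label template and one pharmacy-held list. Some stock may be discarded early because of the common expiry date. Section 11.1.1 ties the label to good manufacturing practice, so it must be confirmed that the trial batch code, backed by the pharmacy list, meets that requirement.

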| STUDY DESIGN: This is a proof-of-concept Phase II clinical trial with three different groups: two groups will receive antichagasic therapy plus 40 or 80 mg/day of ATO, respectively. The third group will receive a placebo plus antichagasic therapy. Patients will first receive conventional antichagasic treatment for two months. After a washout of two weeks (or until normalization of liver enzymes), treatment with atorvastatin or placebo will be initiated for two months. These doses were chosen to minimize false negative results, thus providing the best hypothesis test and maximizing the pharmacodynamic effect on inflammation and cardiac and endothelial function. In addition, the treatment sequence aims to minimize adverse reactions that could be caused by the eventual combination of antichagasic drugs with atorvastatin. Study subjects will be randomized, and the three groups will be double-blinded (both clinical investigators and subjects will be blinded) to ATO or placebo. However, antichagasic therapy will be open-label. In addition, qPCR and the other laboratory evaluations, as well as ECG and 2D echocardiograms, will be performed with the clinical investigators blinded to ATO or placebo allocation.

As mentioned above, this study will be conducted at four centers: 1) Hospital San Juan de Dios and 2) Hospital Felix Bulnes in Santiago, Metropolitan Region, 3) Hospital [name] in Viña del Mar, and |

4) Hospital San Martin de Quillota, Valparaiso Region.

**ABSTRACT:** Cardiac complications, including heart failure and arrhythmias, are major causes of disability and death in Chagas disease (CD). We postulate that statins ameliorate vascular and cardiac inflammation in patients with chronic CD, contributing to the recovery of endothelial and cardiac function and thereby improving the efficacy of antichagasic therapy.

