## 8.2. Secondary goals:

8.2.1. To evaluate the efficacy of the combination of ATO and antichagasic therapy to decrease:

- Inflammation, as measured by plasma levels of the cytokines, TNF- $\alpha$ , IFN- $\gamma$ , IL-10, IL-1B, IL-4, and IL-17A.
- Endothelial activation, as measured by plasma levels of sCAM: sE-selectin, sICAM-1, and sVCAM-1.
- Cardiac damage and function: measured by plasma levels of BNP, cTnT, 12-lead resting ECG (heart rate, QT segment duration, and electrical conduction changes determined by QRS segment duration and morphology), and 2D echocardiogram (ejection fraction).

8.2.2. To determine the safety and tolerability of the combination of ATO with antichagasic therapy, measured by the incidence of AEs (e.g., rhabdomyolysis) and treatment discontinuation.

8.2.3. To evaluate the treatment response to the combination of ATO with antichagasic therapy, as measured by quantitative PCR and serology, over a 10-month follow-up period.

8.2.4. To determine the degree of therapy adherence by measuring drug accountability throughout the study.

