#### **9.5. Duration of the study and duration of subject participation:**

The total duration of patients' participation in the study will be twelve months, considering two weeks for screening and evaluation according to PCC guidelines and eight weeks of treatment with the antichagasic drugs. The administration of ATO and placebo will continue for an additional eight weeks in their respective groups. There will be follow-up visits up to 12 months after the start of treatment (see appendix for a graphical presentation of the study design).

Following voluntary written informed consent, patients will begin a 14-day evaluation phase. Once the patient is randomized and treatments are initiated, they will have follow-up visits during the treatment phase of the study on days 30, 60, 120, and 180, with a two-week rest period or until normalization of liver enzyme levels ( $\pm$  four-day allowable window), and three visits after the end of treatment (EOT) on days 180, 240 and 360 ( $\pm$  14-day allowable window). In addition, patients will be advised to return on any day during the follow-up period if they have any medical incidents or AEs.

Recruitment is expected to be completed within 24 months from the start of recruitment. Therefore, the time frame between the first patient entering (FPI) and the last patient leaving (LPO) is 36 months. However, the total duration of the study is estimated at 48 months, from the initiation phase to the final study report.

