| Pregnancy test                            | x         |          |           |    |                | x                | x                |     |
| Serology                                  | x         |          |           |    |                |                  |                  | x   |
| Laboratory                                | x         | x        | x         | x  | x              | x                | x                | x   |
| Quantitative PCR                          | x         |          |           |    | x d |                  |                  | x   |
| Biomarkers b                   |           | x        |           | x  | x              |                  |                  | x   |
| Focused Physical Examination c | x         | x        | x         | x  | x              | x                | x                | x   |
| Adverse Events                            |           |          | ←-----→   |    |                |                  |                  |     |
| Drug Accounting                           |           | x        | x         | x  | x              |                  |                  |     |

aLaboratory parameters will include: hemoglobin, total white blood cell count, differential white blood cell count, and platelet count. Laboratory biochemical parameters will include: CK, ALT, AST, GGT, alkaline phosphatase, total and direct bilirubin, a lipid profile: total cholesterol, c-HDL, and c-LDL, triglycerides, fasting blood glucose, and creatinine;

bBiomarkers: BNP, cTnT, IFN-γ, IL-1β, IL-4, IL-17A, e IL-10, sICAM-1, sVCAM-1, sE-selectin;

cPhysical examination focused only on the evaluation of adverse events.;

dPCR testing at these time points will be done with a single 10 ml sample;

eECGs will be performed at these visits only in case of previously identified abnormalities

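### Both schedule tables stop drug accounting at day 120, although section 11.1.1 requires a day-180 count and, at nominal timing, every stated atorvastatin/placebo course ends after day 120

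*Protocol*

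**What the plan says.** **When tablets are counted.** Section 11.1.1 states: "At each visit, the patient will be required to bring all remaining study medications at the 30th, 60th, 120th". It continues with the day-180 visit and gives the purpose as checking compliance and accounting for medication. The row "Drug Accounting" in the section 9.6 table has marks at days 0, 30, 60 and 120 and none at day 180. The Study Flowchart in the Summary has the same four marks. Both tables place day 180 under the treatment period.

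**What the counts are for.** Section 8.2.4 sets a secondary goal: "To determine the degree of therapy adherence by measuring drug accountability throughout the study".

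**When the randomised drug is taken.** Section 9.3 states: "Patients will first receive conventional antichagasic therapy for two months". The Summary and section 9.5 give this phase as eight weeks. The Summary then puts the interval before atorvastatin or placebo as "After a washout of two weeks (or until normalization of liver enzymes".

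**How long the randomised drug is taken.** The protocol gives three lengths:
- Summary, study design: "treatment with atorvastatin or placebo will be initiated for two months".
- Section 9.5, with the same length in the Summary's paragraph on study duration: "The administration of ATO and placebo will continue for an additional eight weeks in their respective groups".
- Section 9.3, at the matching point in its description: "four months. These doses were chosen to minimize false negative results", that is, a four-month course.

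**The concern.** Sites commonly work from the schedule table, and the case report form is commonly built from it. If the table governs, the open-label antichagasic course that all three arms receive is counted to its end. The blinded course that the trial compares is counted once, part-way through.

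Doses missed after day 120 would then leave no tablet record, and a count not taken at the time cannot be recovered later. At stake is the adherence objective in section 8.2.4. So, possibly, is the identification of deviations for the per-protocol population in section 12.3.

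**Working it through.** The protocol gives no figure for the share of the course covered by counts, so there is none to reproduce. The check sets the last count against the end of the randomised course.

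**Inputs**
- Antichagasic phase: 56 days (eight weeks; Summary, section 9.5) or 60 days (two months; Summary, section 9.3).
- Washout: 14 days at least, longer if liver enzymes have not normalised.
- Atorvastatin/placebo course: 56 days (eight weeks), 60 days (two months) or 120 days (four months at 30 days each).
- Last count: day 120 in the tables, day 180 in section 11.1.1.

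**Start** = antichagasic days + washout: 56 + 14 = day 70, or 60 + 14 = day 74.

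**End** = start + course length. **Uncounted days** = end − last count.

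| Course | Start | End | Uncounted after day 120 | Uncounted after day 180 |
|---|---|---|---|---|
| 56 days | 70 | 126 | 6/56 = 11% | 0 |
| 56 days | 74 | 130 | 10/56 = 18% | 0 |
| 60 days | 70 | 130 | 10/60 = 17% | 0 |
| 60 days | 74 | 134 | 14/60 = 23% | 0 |
| 120 days | 70 | 190 | 70/120 = 58% | 10 days |
| 120 days | 74 | 194 | 74/120 = 62% | 14 days |

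Every nominal end falls after day 120. A day-180 count closes the gap for the eight-week and two-month courses, but not for the four-month course.

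**Visit window.** Section 9.5 allows four days either way. On the most favourable reading (washout cut to 10 days, visit held on day 124), a 56-day course after 56 antichagasic days ends on day 56 + 10 + 56 = 122 and is just covered. With 60 antichagasic days, the same reading gives day 60 + 10 + 56 = 126, which is not covered. The window therefore rescues one narrow case only.

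**Later start.** The wait for liver enzymes has no upper limit, so the gap can exceed the table above. As an illustration only, a start on day 90 leaves 120 − 90 = 30 days counted. The uncounted share is then 26/56 = 46% of an eight-week course or 90/120 = 75% of a four-month course. Day 90 is an assumption and does not appear in the protocol.

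**The case against.** The strongest reply is that section 11.1.1 already provides the missing count. It says tablet accounting is monitored at each visit, and it names day 180. On that view the defect is one absent mark, repeated in two tables. This stands in part: the protocol does not lack a final count, it contradicts itself about one. The contradiction still matters, because both tables agree with each other against the text and the protocol does not say which prevails.

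A second reply is that early stopping is visible elsewhere. Treatment discontinuation is measured under section 8.2.2, subjects are interviewed about adverse events at each visit, and visits continue to day 360. This also stands in part. Those records can show a patient who stops, but they do not replace a tablet count for doses missed by a patient who is nominally still on treatment.

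A third reply is that the consequences are limited, and this stands in full. Adherence is a secondary goal and the per-protocol analysis is secondary (section 12.4). Section 12.3 defines that population by the absence of significant deviations and gives no adherence threshold. How adherence is calculated, and how it feeds into the per-protocol set, may properly be left to the statistical analysis plan.

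**Conclusion.** The tables and section 11.1.1 conflict. At nominal timing, the tables leave the end of the randomised course without a tablet count under every course length in the protocol: 11–23% of an eight-week or two-month course, and 58–62% of a four-month course. These figures assume a 14-day washout, visits on their nominal days and 30-day months. Most of the spread comes from the unresolved course length, and this review does not say which length is right.

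A reader might infer more than the protocol supports:
- **That up to three quarters of the course goes uncounted.** This needs a start around day 90, which is possible but stated nowhere.
- **That adherence will be overstated and the per-protocol comparison diluted.** The direction cannot be derived from the protocol, and section 12.3 does not tie membership to tablet counts. What can be said is that relevant deviations may go unseen.
- **That a day-180 mark alone settles the matter.** It does not if the course lasts four months.

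The intention-to-treat primary analysis and the sample size are untouched. The correction is still worth making, because it affects what sites collect and works only if made before the visits take place.

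**What to change.** 1. Mark drug accounting at day 180 in the Summary flowchart and in the section 9.6 table, to match section 11.1.1.
2. Reconcile the two tables, section 11.1.1 and the differing atorvastatin/placebo course lengths (Summary, sections 9.3 and 9.5), so that a final count falls at or after each patient's last randomised dose. In doing so, settle the status of day 180, which section 9.5 lists both among the treatment-phase visits and among the visits after end of treatment.

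The first step costs one mark in each table and the matching case report form page, at a visit that already takes place. The second is an editorial amendment if the reconciled course ends by day 180. If it ends later, the final count must move to a later contact, such as the existing day-240 visit.
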